#### Compositional data analysis

To analyse the relative proportion of time spent in different activities, we will also investigate the association between movement behaviour (exposure), urban green and blue space (exposure) and cognitive health (outcome) by implementing a compositional data analysis approach. Having access to accelerometry, GPS and GIS enable investigations that are focused both behaviourally (part 1) and geographically (part 2).

Part 1—behaviour focused; will examine:

(1a) during waking hours, how is time spent in one movement behaviour relative to others (ie, sedentary behaviour, light physical activity and moderate-to-vigorous physical activity) and associated with cognitive health?

(1b) how does the risk of cognitive decline change, when the time spent in specific movement behaviours (ie, sedentary behaviour, light physical activity and moderate-to-vigorous physical activity) are redistributed across waking hours?

Part 2—addition of geographical location (green and blue space); will examine:

(2a) during waking hours how is time spent in one movement behaviour relative to others (ie, sedentary behaviour in green and blue space, sedentary behaviour everywhere else, light physical activity in green and blue space, light physical activity everywhere else, moderate-to-vigorous physical activity in green and blue space and moderate-to-vigorous physical activity everywhere else) and associated with cognitive health?

(2b) how does the risk of cognitive decline change, when the time spent in specific movement behaviours (ie, sedentary behaviour in green and blue space, sedentary behaviour everywhere else, light physical activity in green and blue space, light physical activity everywhere else, moderate-to-vigorous physical activity in green and blue space and moderate-to-vigorous physical activity everywhere else) are redistributed across waking hours?

Multivariate analysis of variance will be conducted to investigate the difference in participant compositions (ie, part 1a and 2a) and the outcome of cognitive health. Compositional data analysis which is based on isometric log-ratio data transformation will then be conducted to model the association of time spent in different movement behaviours during waking hours and cognitive health.^64 65^ Minute-by-minute isotemporal substitutions will be made from one behaviour to another while holding the remaining behaviours constant, to model change in cognitive health. Adjustments for potential confounders and mediators will be made and includes age, sex, socioeconomic status, lifestyle behaviours (eg, smoking, drinking), disability, car ownership etc.

To control for multiple comparisons, the false discovery rate correction will be applied using the Benjamini-Hochberg procedure, adjusting for the total number of analyses conducted.

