### Study procedure

After completing the battery of cognitive tests, NICOLA-HCAP participants will be invited to participate in the current study by the NICOLA-HCAP researcher if they meet the inclusion criteria detailed above.A short description of the current study and what is expected of potential participants will be verbally provided by the NICOLA-HCAP researcher, and participants will be provided with a paper copy of the participant information sheet and participant invitation letter.Potential participants will have the opportunity to ask the NICOLA-HCAP researcher questions relating to any element of the current study.At this stage, if participants verbally agree to participate in the current study, the NICOLA-HCAP researcher will provide them with a study pack. This pack contains two consent forms, two monitors (an accelerometer and a GPS device on an elasticated waist band), a monitor instruction sheet and a GPS charger.If the potential participant requires more time to consider their participation, the NICOLA-HCAP researcher will only leave a study pack if the participant agrees that this is acceptable. It should be noted that leaving a study pack does not mean that the individual must participate in the current study, they are free to refuse participation or to withdraw at any time without providing a reason.Participants will have the opportunity to read through the information and to familiarise themselves with the project before a project researcher contacts them via telephone approximately 1–3 days after their NICOLA-HCAP visit. This call aims to: (1) ensure that the participants understand the procedures; (2) provide participants with an opportunity to ask questions and (3) ensure that a standardised measurement approach is undertaken. If at this stage the participant wishes to withdraw, they are free to do so, and the researcher will arrange collection of their study pack. If they are willing to participate, they will be asked to wear both monitors on the elasticated waist belt for seven consecutive days.If a participant did not agree to a study pack being left at their home but they did agree to a researcher phoning to discuss their potential participation, the researcher will make contact via telephone 1–3 days following the NICOLA-HCAP study. If at this stage the participant agrees to participate, a researcher will arrange a time to drop/post a study pack to their home.During the 7-day monitoring period, participants will be asked to wear the monitors on an elasticated belt during waking hours (ie, remove to go to bed). The devices may also be removed when undertaking any water-based activities. To reduce participant burden, the research team will only contact participants once by telephone to ensure that they are not having any issues and to answer any questions that they might have. The participants will also have been provided with a telephone number to enable them to contact the research team on with any queries they may have.Following the 7-day monitoring period, the research team will contact the participant to arrange a date/time to collect the monitors along with one signed consent form from the participant’s home.Alternatively, if the participant would prefer to have a postal return the research team will provide a pre-paid return package.

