### Longitudinal follow-up

Participants will be followed up through a second wave of data collection in conjunction with the second wave of NICOLA-HCAP in 2026. Participation in wave 2 will be offered to any surviving members of the wave 1 sample who are not living in a nursing home, can provide written informed consent and have been deemed to have the capacity to consent. In addition, a random sample of new participants (≥65 years) who have been recruited to NICOLA and subsequently NICOLA-HCAP through a sample refresh and who meet the inclusion/exclusion criteria will also be invited to participate. The same study procedures outlined above will be followed. This will provide a longitudinal integrated dataset which includes: (1) physical activity behaviour; (2) environmental exposure data; (3) geospatial environmental data; (4) biological data and (5) a range of cognitive health outcomes. Longitudinal high-resolution spatial datasets will be created facilitating investigations into the influence of the urban environment on cognitive health over time. Wave 2 of this study and NICOLA-HCAP have been planned for 2025/2026, pending the successful obtainment of funding. Please see online supplemental figure 1.

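### Compositional questions 1b and 2b ask about risk of cognitive decline, but the analysis defines no decline outcome; run on wave 1 data, it yields a cross-sectional difference

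*Protocol article*

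**What the plan says.** The Compositional data analysis section of the protocol article sets out four questions. Questions 1a and 2a ask how relative time use is associated with cognitive health. Question 1b asks "how does the risk of cognitive decline change, when the time spent in specific movement behaviours" are redistributed over waking hours, and 2b asks the same with each behaviour split by whether it takes place in green and blue space.

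The same section names its exposures and outcome as movement behaviour, "urban green and blue space (exposure) and cognitive health (outcome"). The model is meant to "model the association of time spent in different movement behaviours during waking hours and cognitive health". Minutes are then moved from one behaviour to another while "holding the remaining behaviours constant, to model change in cognitive health".

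On timing, Study procedure states: "After completing the battery of cognitive tests, NICOLA-HCAP participants will be invited to participate in the current study". A telephone call follows about one to three days after the visit. Those still willing are then told that "they will be asked to wear both monitors on the elasticated waist belt for seven consecutive days". On repeat assessment, Longitudinal follow-up states: "Wave 2 of this study and NICOLA-HCAP have been planned for 2025/2026, pending the successful obtainment of funding".

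**The concern.** Risk of decline implies within-person worsening, a criterion for it and a period over which it is observed. The model described has none of these. A fitted substitution effect would be a contrast between people who use their time differently.

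Poorer cognition can itself reduce activity, and a contrast in current level also carries long-standing differences in ability. If such a contrast is reported as the change in risk of decline from moving so many minutes into activity, a cross-sectional association becomes a preventive claim. The Introduction says the findings should inform preventive strategies and policies, so the label matters.

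**Working it through.** No arithmetic applies: the plan gives no figure for this analysis. The only power calculation in the article belongs to the mediation test. The check sets the question, the model and the timing side by side.

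**1. What the stated model estimates.** Let z be the log-ratio coordinates of a person's time use, C the adjustment variables and Y the cognitive outcome:

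E[Y | z, C] = b0 + b'z + g'C

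Moving minutes from one behaviour to another changes z to z*, and the substitution effect is b'(z* − z). If Y is a score from one assessment, this is the expected difference in that score between people with compositions z* and z and the same C. The phrase "to model change in cognitive health" can then mean only a model-predicted difference. If Y is impairment status at one assessment, the corresponding quantity is a difference in prevalence.

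**2. What questions 1b and 2b need.** They need an outcome observed after the behaviour and a reference for where the person started, for example E[Y2 | z1, Y1, C] with the subscript denoting wave, or the probability of a defined decline event between waves. The section states neither. Its adjustment list is open-ended, but prior cognition is not among the items named, nor is it named in the separate Confounders section.

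**3. Order of measurement at wave 1.** Battery first, then invitation, then a call about one to three days after the visit, then seven days of wear. Every wave 1 HCAP score therefore precedes the measured behaviour, and none can record decline after it.

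**4. Other possible sources of a decline outcome.**

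| Source | Where in the article | Does it answer 1b/2b? |
|---|---|---|
| NICOLA Waves 1 and 2 to HCAP | Mediation analysis | Gives change, but change that ended before the monitoring week; assigned only to mediation |
| IQCODE informant rating | Table 3 | Rates decline up to the time of the HCAP informant interview, so it looks backward; not assigned to this analysis |
| Algorithmic classification of impairment or dementia | Cognitive health outcome variables | Gives status, so prevalence at wave 1 |
| Wave 2 HCAP | Longitudinal follow-up | Could answer it, if funded; not assigned to this analysis |

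**5. Wave 2 in more detail.** Wave 2 also brings in newly recruited participants, who would have only one HCAP assessment by then. The Abstract's figure of 400 at each wave is therefore not the number with two assessments. That number is not given; it cannot exceed the wave 1 sample.

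**6. Comparison with the other analyses.** Total effect analysis names previous cognitive function among the causes of physical activity. Mediation analysis specifies latent change scores to establish temporal order. Neither device is carried into the compositional section.

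**The case against.** A reader might infer that the plan's outcome is a single cognitive assessment, so that the study can show only level and can observe no decline at all. The documents do not support this. The compositional section fixes no wave and no instrument. The design is longitudinal, and a second wave with the same procedures is planned. Earlier NICOLA cognition exists, and an informant measure of decline is in the battery. A two-wave cohort may properly pose a question that its second wave will answer. The limitation to level or prevalent status therefore applies to wave 1 use of battery scores or diagnoses, not to the plan as a whole.

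Three further points are fair:

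- The article is condensed, and the wave and score for each model may be set out in a fuller document. The absence of a decline criterion would be weak ground if it stood alone. It does not: the questions name one outcome, and the analysis offered to answer them names another.
- The gap between battery and monitoring is short, and for the total-effect analysis the authors assume that the seven days represent usual activity. Reverse causation arises mainly from cross-sectional use, not from those few days. That is correct, but it does not turn a wave 1 score into an outcome that follows the exposure.
- Much of the section uses the language of association, and the word change can be read as predicted change under reallocation. That softens the substitution sentence but leaves the risk-of-decline wording in 1b and 2b as it is.

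**Conclusion.** The point holds in conditional form. Questions 1b and 2b ask about risk of cognitive decline, while the outcome and model given for them contain no decline outcome, no follow-up and no prior-cognition term. Applied to wave 1 data, the analysis gives a cross-sectional difference in level or in prevalent impairment, open to reverse causation. The retrospective sources do not repair this, because they describe decline up to the HCAP assessment. Wave 2 could repair it but is unfunded in the document and not tied to these questions.

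The size is qualitative: two of the four compositional questions, for the whole wave 1 sample (target about 400). How far a level contrast would differ from a true effect on decline cannot be worked out from the documents. The conclusion assumes that the model is run as described and, for wave 1, that the outcome is a battery score or the algorithmic classification. It should be corrected, because it governs what may be claimed, but it does not invalidate the analysis as a study of association.

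**What to change.** For wave 1, reword 1b, 2b and the substitution sentence so that the target is *the predicted difference in cognitive health (or in prevalence of algorithm-defined impairment) for a given reallocation of time*.

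Keep the decline question only for participants with both HCAP waves, and define decline for that analysis. One suitable form takes the wave 1 time composition as exposure and the wave 2 score as outcome, conditional on the wave 1 score from the same tests. State that no decline claim will be made from this analysis if wave 2 does not take place.

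The cost is the wording of two questions and one sentence, plus a short statement on the two-wave analysis. No data are needed beyond those already planned. The downside is a more modest wave 1 conclusion.

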## Introduction

 Maintaining cognitive health and preventing dementia is a global health priority due to the rapidly ageing nature of the population and the increased number of individuals living with mild cognitive impairment. In the UK in 2019, approximately 900 000 people were living with dementia (mild, moderate and severe) with this figure projected to increase by 80% to approximately 1.6 million by 2040.^1^ This stark increase in dementia cases will bring a significant economic (eg, healthcare and social care) and societal (eg, unpaid care from friends/relatives) burden. Annual costs have been estimated at £94.1 billion in 2040, which will be a significant increase from £34.7 billion in 2019.^1^ Globally, the estimated costs of dementia are projected to rise to US$2 trillion annually by 2030.^2^ These figures highlight the urgent need for the development and implementation of effective prevention strategies and policies to target the established modifiable risk factors of dementia.^3 4^

In 2020, the Lancet Commission highlighted 12 modifiable risk factors that account for around 40% of dementias worldwide, which could theoretically be prevented or delayed.^4^ Of the 12 modifiable risk factors for dementia, seven could be positively influenced through the provision of healthy urban environments (namely, hypertension, obesity, depression, social isolation, physical inactivity, diabetes and air pollution). Healthy urban environments have the potential to provide population level benefits.^3^

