The design of the urban environment could both negatively and positively impact cognitive health. For example, poor-quality, high-density, urban environments are associated with potentially harmful levels of traffic, air and noise pollution and environmental degradation, all of which have adverse effects on human health.^5^,^8^ A recent systematic review reported that higher levels of ambient air pollution were consistently associated with lower levels of global cognitive function, while extended exposure to high levels of particulate matter smaller than 2.5 micrometres (PM_2.5_) was associated with accelerated cognitive decline in several longitudinal studies. PM_2.5_ levels were associated with higher dementia incidence across several studies.^9 10^ Conversely, certain urban design features such as walkable and cycle friendly environments, mixed land use, access to green space and public spaces, proximity to community resources and access to public transport have the capacity to reduce car dependency, promote active transport and physical activity, and, as a consequence, better cognitive health outcomes.^311^,^13^ These urban environment factors have the potential to facilitate mechanisms such as reductions in noise and air pollution, less sedentary behaviour and increased levels of physical activity which improves cardiometabolic health, reduces risk of obesity and reduces inflammatory markers and oxidative stress.^311^,^13^ For example, a systematic review and meta-analysis of longitudinal studies reported that physical activity was associated with an 18% reduction in dementia risk.^14^

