### Confounders

Confounders such as age, sex, education, employment status, smoking, diet, cardiovascular risk factors, depression, years at home address will be accounted for.

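### The compositional models adjust for mediators as well as confounders, although they ask what happens when time is redistributed and declare no direct-effect estimand

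*Protocol article*

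**What the plan says.** The Compositional data analysis section treats both movement behaviour and green and blue space as exposures, with cognitive health as the outcome. Questions 1b and 2b ask "how does the risk of cognitive decline change, when the time spent in specific movement behaviours" are redistributed over the waking day. Minute-by-minute isotemporal substitution is then used to model the resulting change in cognitive health. The covariate rule for these models is: "Adjustments for potential confounders and mediators will be made and includes age, sex, socioeconomic status, lifestyle behaviours". The list goes on to smoking and drinking (as examples of lifestyle behaviours), disability and car ownership, and it is open-ended. It does not say which items are confounders and which are mediators.

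Three other places bear on this:

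- **Total effect analysis** (MVPA on MMSE): the adjustment set is to come from a DAG by d-separation and the backdoor criterion.
- **Confounders:** a short general list, tied to no model: "Confounders such as age, sex, education, employment status, smoking, diet, cardiovascular risk factors, depression, years at home address will be accounted for".
- **Introduction:** of the modifiable dementia risk factors, "seven could be positively influenced through the provision of healthy urban environments (namely, hypertension, obesity, depression, social isolation, physical inactivity, diabetes and air pollution"). It also credits urban design with "increased levels of physical activity which improves cardiometabolic health, reduces risk of obesity and reduces inflammatory markers and oxidative stress".

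**The concern.** Asking how risk changes when minutes move from one behaviour to another is, on its face, a question about the whole consequence of the move, including whatever passes through intermediate variables. A model that holds those intermediates fixed answers a narrower question: what would change if the behaviour changed but its downstream effects did not.

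The substitution estimates are likely to be read as the effect of changing behaviour or of spending time in green and blue space. If mediators are in the model, the mediated part is missing and the reader is not told. The total effect analysis also studies activity and cognition but selects covariates so as to leave mediators out. Results from the two could then differ because one is total and the other partly direct, and that difference might be mistaken for a substantive finding.

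**Working it through.** **The plan's own figures.** The plan attaches no figure to this choice. Its one power statement (about 462 participants for power 0.8, both paths 0.14) belongs to the mediation analysis. Simulation reproduces it (0.79 at 462, assuming two-sided 5% and no direct effect), but the point here does not depend on it.

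**The three analyses side by side.**

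| Analysis | Question | Covariate rule |
|---|---|---|
| Total effect | Total effect of MVPA on MMSE | DAG and backdoor criterion |
| Mediation | Environment to cognition through lifestyle behaviours | Role of each covariate set by the proposed mechanism |
| Compositional | Change in risk when time is redistributed | Confounders and mediators together |

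Only the third puts mediators into the covariate set without naming a direct effect as its target.

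**What the rule does, in a linear model.** Let X be the exposure, M a mediator and U an unmeasured cause of both M and the outcome Y, with X, U and the errors independent and of variance 1:

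- M = aX + gU + error
- Y = cX + bM + gU + error

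The total effect is c + ab. A model without M recovers it. Given X and M, the best linear prediction of U is g(M − aX)/(1 + g²), so in a model with M the coefficient of X is c − a·g²/(1 + g²). Two things follow:

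1. With g = 0, adjustment returns c. The indirect part ab is lost.
2. With g ≠ 0, adjustment does not return the direct effect c either.

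**Illustration, with assumed values.** The document gives no path values for these covariates. The 0.14 is borrowed from the mediation section, where it is the assumed size of each mediation path. Using it for c, the upper value of 0.5 for a and b, and g = 0.3 are all assumptions.

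| a = b | c | g | Total c + ab | Adjusted for M | Loss |
|---|---|---|---|---|---|
| 0.14 | 0.14 | 0 | 0.14 + 0.0196 = 0.1596 | 0.14 | 0.0196/0.1596 = 12% |
| 0.14 | 0.14 | 0.3 | 0.1596 | 0.14 − 0.14 × 0.09/1.09 = 0.128 | 20% |
| 0.5 | 0.14 | 0 | 0.14 + 0.25 = 0.39 | 0.14 | 0.25/0.39 = 64% |
| 0.5 | 0.14 | 0.3 | 0.39 | 0.14 − 0.5 × 0.09/1.09 = 0.099 | 75% |

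Simulation with 500,000 observations per row gave adjusted coefficients of 0.143, 0.127, 0.141 and 0.101, in line with the formula. The losses are toward zero because all paths were given the same sign; with mixed signs the error could go the other way. The table shows the mechanism and how widely the result depends on unknown values. It does not estimate the bias in this study.

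**The case against.** The case on the other side has real force, and most of it narrows the point.

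- **The covariates actually named are largely ordinary confounders.** Age, sex, socioeconomic status and car ownership raise no difficulty. Disability may well precede activity; the total effect section treats physical impairments as causes of it. The mediation section tests lifestyle behaviours as mediators of the environment effect, but where the article gives examples of those it names physical and social activity, whereas the compositional section names smoking and drinking. The shared label is weak evidence that these items are mediators. This stands: the defect is the stated rule, not that the named items are shown to be mediators.
- **The section speaks of association, and only another analysis is headed as a total effect.** That is fair as to vocabulary. But questions 1b and 2b ask what changes under redistribution, and nothing there declares a direct effect, which is what would justify conditioning on mediators.
- **The analyses differ anyway,** since one works with MVPA minutes and the other with shares of the waking day. That is no defect. The undeclared switch from total to partly direct is.
- **It is a condensed article.** Detail left out would be no finding, but here the rule is stated.

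A reader might go further and infer that the whole plan is biased by mediator adjustment, because the Confounders section lists cardiovascular risk factors and depression, which the Introduction places on the pathway. The document does not support that. The list is illustrative and tied to no model, and nothing says that it overrides the covariate rules of the total effect and mediation analyses. In people aged 65 or over these conditions may also precede and limit activity, so they can be confounder, mediator or both; timing of measurement has to decide.

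**Conclusion.** The concern holds for the compositional and isotemporal-substitution models. As written, the covariate rule conditions on mediators while the questions concern the consequence of redistributing time and no direct-effect estimand is named. Followed literally, it removes whatever part of the effect is mediated and can bias the rest if mediator and outcome share an unmeasured cause. It also leaves the two activity analyses estimating different quantities without saying so.

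The size cannot be derived from the document. The losses of 12% to 75% shown above rest entirely on assumed paths. Translating them into a loss of power would mean treating the mediation section's per-path 0.14 as a total effect and inventing a mediated share; neither has support.

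Two further inferences should not be drawn. The total effect and mediation analyses are not shown to be biased, for the reasons given above. Nor is deprivation omitted from the plan: the total effect section names it, the compositional section adjusts for socioeconomic status, and the general confounder list does not claim to be complete.

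**What to change.** In the Compositional data analysis section:

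1. State the estimand of the substitution models.
2. Replace the reference to confounders and mediators with a confounder set derived from the DAG, separately for movement behaviour and for green and blue space, and excluding mediators of the exposure in question.
3. Report any mediator-adjusted model only as a sensitivity analysis labelled as a direct effect, with its assumption of no unmeasured mediator-outcome confounding stated.
4. Where the set draws on the general Confounders list, include cardiovascular risk factors and depression as confounders when they were measured before the exposure. Where only concurrent values exist, show results with and without them. Dropping them outright could leave confounding by existing illness.

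The cost is a change of wording, a DAG extended to the second exposure, and some extra model runs. No new data collection is needed, because step 4 covers the case where no earlier values are available. The change should be made before these models are run.
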